**Methods:**

This is a feasibility study and randomized control trial of a checklist and intensive peer intervention for hospitalized PWID with SIRI admitted to UAB Hospital. We will recruit 60 PWID who will be randomized to one of 4 groups (SIRI Checklist, SIRI Checklist + Enhanced Peer, Enhanced Peer, and Standard of Care). Results will be analyzed using a 2x2 factorial design. We will use surveys to collect data on drug use behaviors, stigma, HIV risk, and PrEP interest and awareness. Our primary outcome of feasibility will include the ability to recruit hospitalized PWID and retain them in the study to determine post-discharge clinical outcomes. Additionally, we will explore clinical outcomes using a combination of patient surveys and electronic medical record data (HIV, HCV testing, MOUD and PrEP prescriptions).

This study is approved by UAB IRB #300009134.

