## Study Objectives and Specific Aims

The overarching objective of this study is to test the feasibility of a SIRI checklist aimed at increasing evidence-based treatment for hospitalized PWID. We will reach this objective through the following AIMS:

Aim 1) Determine the feasibility of a pilot SIRI Checklist and Intensive Peer Intervention for hospitalized PWID to increase uptake of OUD treatment and PrEP and facilitate linkage to community-based services. Feasibility will be measured via recruitment and retention of participants, completion of each portion of the intervention (baseline surveys and follow up assessments), and ability to contact patients post-discharge for intensive Peer support and/or completion of follow up assessments. We will also evaluate the ability to extract documentation of the SIRI Checklist and Peer documentation provider notes.

Aim 2) Quantify risk behaviors in a contemporary Southern cohort of PWID and evaluate Secondary Patient-Centered Outcomes for participants enrolled in the study. We will use validated tools to survey hospitalized PWID on substances used and methods of use, HIV risk behaviors, and substance use stigma. We will also explore the preliminary impact of this low-tech checklist on evidence-based services, such as initiation of buprenorphine, PrEP, HCV screening, and referral to community care. These measures will be compared with treatment groups that do not receive the SIRI Checklist.

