The third progression criterion we will employ is participant safety and adverse effects. For this criterion, we will use a Data Safety Monitor model (DSM). A DSM will be designated as an independent faculty member charged with ensuring that the safety of study subjects is protected and that the scientific goals of the study are being met. To support those purposes, the DSM will review any proposed amendments to the study protocol, perform expedited monitoring of all serious adverse events, perform ongoing monitoring of drop-outs and non-serious adverse events, determine whether study procedures should be changed or the study should be halted for reasons related to the safety of study subjects, and perform periodic review of the completeness and validity of data to be used for analysis of safety and efficacy. The DSM will also ensure subject privacy and research data confidentiality.

Finally, to evaluate signals of efficacy, we will evaluate whether participants have received the recommended services that are included in our ShaPe intervention, such as HIV and HCV screening, MOUD prescriptions, and HIV PrEP referrals. Specifically, we will evaluate whether these measures are enacted after the inclusion of the smart phrase text. This data will be collected via provider documentation and the 3-month follow-up survey with participants.

These progression criteria will be used to determine protocol adjustments to be made prior to enacting a larger study. For example, should the recruitment timeline be insufficient, we will evaluate whether the intended population is large enough for a study to be conducted and if so, how we could better identify eligible participants to be enrolled in the study. Adjustments to the smart phrase text will be made to account for under utilization in patient notes and insufficient delivery of recommended services to participants. We will also determine whether the number lost to follow-up reflects adequate usage and efficiency of CTS. In the event that these adjustments are not adequate for a larger study to be conducted, we will establish a new protocol for study.

All amendments and changes to protocol must be approved by UAB IRB before enacted.

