#### Sampling and Recruitment Procedures

Participants will be recruited following hospitalization for SIRI at UAB Hospital. Our research coordinator will meet biweekly with the Addiction Medicine social worker and/or nurse practitioner, to identify eligible PWID who express interest in study participation. The research team member will then discuss the study with those who are eligible, and if the participant expresses interest, the informed consent process will be completed (appendix 3). We will provide phones for participants who do not have access to a phone. The participant will then complete the survey used to accomplish Aim 1. Following survey completion, the participant will be randomly sorted using a 2x2 Factorial Design, into one of the four groups: SIRI Checklist, SIRI Checklist + Enhanced Peer, Enhanced Peer, and Standard of Care. Randomization will be performed in advance using blocks of n = 4 and n = 8. A total of 60 participants will be recruited, 15 per group, which is in alignment with sample size guidance for pilot and feasibility studies [24]. For incentive, patients will receive a $30 gift card at enrollment, as well as a $30 gift card at the 3-month follow up (Fig. 2).

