### Analysis

To evaluate our primary aim, feasibility will be evaluated through time and number of eligible participants required for participant recruitment, participant retention, and completion rates. Acceptability will be evaluated through patient enrollment and provider survey responses towards the SIRI checklist and Intensive Peer.

As a secondary outcome, we will explore the participant data and summarize sociodemographic and clinical factors of participants using descriptive statistics (measures of central tendency, dispersion, and distribution) and confidence intervals. Clinical factors will include initiation of buprenorphine, PrEP, HIV and HCV screening, and referral to community care. Lastly, we will evaluate the provider survey data to identify overall trends in provider responses.

These results are planned for presentation at national conferences and inclusion in manuscripts for publication in high impact journals.

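### The efficacy-signal criterion has no comparator and no reading of the peer factor, and neither it nor the Analysis section carries through the randomised 2x2 comparison promised elsewhere

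*Protocol article*

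**What the plan says.** The article makes four statements about how service outcomes will be assessed.

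- **Progression criteria (Aim 2: Secondary Patient-Centered Outcomes).** Signals of efficacy are the fourth criterion for moving to the main trial. They concern receipt of the recommended services, "such as HIV and HCV screening, MOUD prescriptions, and HIV PrEP referrals". The next sentence narrows this: "Specifically, we will evaluate whether these measures are enacted after the inclusion of the smart phrase text". No comparison group is named.
- **Abstract, Methods.** "Results will be analyzed using a 2x2 factorial design".
- **Study Objectives and Specific Aims, Aim 2.** After listing service outcomes such as buprenorphine, PrEP, HCV screening and referral: "These measures will be compared with treatment groups that do not receive the SIRI Checklist".
- **Analysis.** For the secondary outcomes the plan is to "summarize sociodemographic and clinical factors of participants using descriptive statistics (measures of central tendency, dispersion, and distribution) and confidence intervals". The same section adds: "Clinical factors will include initiation of buprenorphine, PrEP, HIV and HCV screening, and referral to community care". No arm or factor contrast is named.

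On design, Sampling and Recruitment Procedures states: "A total of 60 participants will be recruited, 15 per group". According to the Intervention section, providers are told to use the smart phrase for participants randomised to the checklist, which is two of the four groups.

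**The concern.** The first and last of these statements do not fit the middle two. Someone who follows the progression criterion counts services delivered after a smart phrase appears in the notes. Someone who follows Aim 2 compares randomised groups. The two readings can lead to different conclusions about the same data.

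The criterion as worded has three weaknesses:

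- **No comparator.** Standard of Care already includes Infectious Diseases and Addiction Medicine consultation, so some services would follow the smart phrase in any case. The only people who show how many are the concurrent participants without the checklist, and the criterion does not use them.
- **It rests on an event after randomisation.** Whether and when the smart phrase is inserted is up to the provider. The article acts on adherence only when it falls below 80%, so some checklist participants may have no insertion to count from.
- **It gives no reading of the peer factor.** The Background hypothesises that the Intensive Peer Intervention also raises service use and linkage. The peer-specific progression criteria concern calls completed, and the comparison in Aim 2 is on the checklist alone. Only the general factorial sentence in the Abstract covers a peer contrast.

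At stake is whether the signal carried into planning the larger study reflects the interventions or the background level of care.

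**Working it through.** **Design figure.** 4 groups x 15 = 60, as stated. On each factor this gives 2 x 15 = 30 v 30. The article bases this number on pilot guidance and gives no power calculation.

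**Inputs from the article**

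- MOUD at discharge under current care: 37% (Standard of Care); about one in three among those with opioid use disorder (Background).
- PrEP: none in a local survey of 20 (Standard of Care).
- Smart-phrase adherence floor: 80%.
- HIV and HCV screening: no background rate given.

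**What a checklist with no effect would show on MOUD.** Assume 37% applies to every checklist participant.

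- All 30: 30 x 0.37 = 11.1 expected (binomial 95% range 6 to 16).
- At 80% adherence: 0.80 x 30 = 24, and 24 x 0.37 = 8.9 expected.

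With no cut-off at all, the chance of at least one MOUD prescription among 30 is 1 - 0.63^30, above 0.9999.

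**If a one-arm cut-off applies.** The cut-offs below are assumed, since Figure 1 is not shown. The chance that an ineffective checklist reaches each one is the binomial upper tail with n = 30:

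| Cut-off | Count needed | Rate 37% | Rate 1/3 |
|---|---|---|---|
| 25% | 8 | 92% | 83% |
| 30% | 9 | 84% | 71% |
| 40% | 12 | 43% | 28% |
| 50% | 15 | 10% | 4% |

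**PrEP.** At 0 of 20 the expected count under no effect is 0. The upper 95% limit for 0 of 20 is 1 - 0.025^(1/20) = 16.8%. The chance of at least one PrEP event in 30 is therefore 0 at a true rate of 0%, 79% at 5% and above 99% at 16.8%.

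**What the randomised contrast would give.** With no effect the expected difference is 0. The 95% half-width at 37% in both groups is 1.96 x sqrt(2 x 0.37 x 0.63 / n):

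- n = 30 per side (factor margin): 1.96 x 0.1247 = 0.244, about 24 points.
- n = 15 per side (single arms): 0.346, about 35 points.

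With a two-sided 5% test (my assumption), power on the 30 v 30 margin against 37% is about 17% for 50%, 43% for 60% and 74% for 70%. The contrast therefore suits an estimate with an interval, not a test.

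**The case against.** The best defence has five parts.

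- **The comparison is planned.** A reader might infer that the randomised 2x2 contrast is never used. The Abstract and Aim 2 rule that out, and a factorial analysis by its nature covers the peer factor. This defence stands. What remains is that the criterion and the Analysis section do not match those statements.
- **No as-treated population is stated.** A reader might take the criterion to exclude participants whose notes lack the smart phrase. Its first sentence speaks of participants receiving services, and the second adds timing. No exclusion is written down, so that reading is unsupported. The dependence on insertion as the reference point remains.
- **A false signal is not shown.** A reader might infer that an ineffective checklist would necessarily pass. That depends on Figure 1. It is plausible for MOUD under a low or absent cut-off and fails for PrEP at 0 of 20. For HIV and HCV screening it cannot be judged. The 37% is also an approximation: its denominator is not given, and opioid use disorder is not an entry criterion. All of this stands, but a cut-off alone would not supply a comparator.
- **This is not a pure go/no-go rule.** The article uses the criteria mainly to adjust the protocol before a larger study, and insufficient delivery leads first to changes in the smart-phrase text. For that purpose, timing after insertion is a sensible delivery measure. This stands and lowers the severity.
- **An article may leave contrasts to an analysis plan.** That is fair for the Analysis section alone, where summaries with confidence intervals would serve if given by randomised group. It does not cover the progression criterion, which states a specific rule at odds with Aim 2.

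**Conclusion.** The concern holds as an inconsistency with a practical consequence. The efficacy-signal criterion has no comparator and no reading of the peer factor, and the Analysis section names no group contrast. Both need reconciling with the Abstract and Aim 2.

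The size is best shown by MOUD: about 11 of 30 checklist participants would be expected to receive it with no checklist effect. This assumes that the 37% applies to all of them, and that the smart phrase is used only in the two checklist groups, as the Intervention section indicates. The chance of passing a one-arm cut-off with no effect runs from 92% down to 10% as the assumed cut-off rises from 25% to 50%, so no single false-signal rate can be claimed.

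Severity is moderate. Feasibility is the primary outcome, clinical outcomes are exploratory, and this is one of four criteria.

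**What to change.** Reword the criterion so that the efficacy signal is the difference in proportions receiving each service, with a 95% confidence interval, by randomised group and regardless of whether the smart phrase was used:

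- checklist (30) v no checklist (30);
- enhanced peer (30) v no enhanced peer (30).

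Show the four cell proportions (15 each) beside these so that any sign of interaction is visible. State the same contrasts in the Analysis section for the service and linkage outcomes, and say that they are exploratory estimates and not tests. Keep the timing of services after the smart phrase as a measure of fidelity only. If Figure 1 holds efficacy cut-offs, align them with this definition.

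The cost is a few sentences and some extra tables, with no added participants or data collection. The downside is that the intervals will be visibly wide, about 24 points either side at 37%.

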To evaluate the transition to the main trial, we will utilize progression criteria around 1) recruitment and retention, 2) protocol adherence, 3) safety and adverse effects, and 4) signals of efficacy [14]. We will utilize the red, amber, green system for progression criteria [20]. (Fig. 1) For recruitment, we expect to encounter 3 to 4 eligible participants monthly, based on previous studies we have conducted within this population. Given that some of these individuals will refuse to participate in the study, we expect to enroll 2 to 3 participants each month. If we maintain recruitment of 2 or more patients per month, we expect to reach our goal of enrolling 60 participants (15 participants for each arm of the study) within 24 months. If recruitment falls below 2 patients per month, we will explore alternate methods for recruitment to improve recruitment rates. If recruitment stalls and no patients are recruited for more than two consecutive months, the trial will terminate. Retention will be determined by documenting the proportion of: participants who complete weekly calls with their peer, peer calls completed, and participants who complete the follow up survey at 3 months. The target retention rate for each of these rention progression criteria is 75% [21].

To ensure adherence to the study protocol, we will monitor patient documentation to determine whether the ShaPe “smart phrase” was utilized in patient notes. We expect that this smart phrase will be included in all participant documentation after implementation. If adherence to the study protocol falls below 80%, we will revisit the protocol with providers to determine whether further training or modifcations are necessary [21].

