### Intervention

This study will test two interventions. The SIRI Checklist will build on the existing standard of care for SIRI by adding a standardized reminder to offer MOUD, HIV risk assessment, and refer to appropriate community-based care. SIRI Checklist was inspired by the iCARE checklist, developed for endocarditis in PWID, but is applicable for all PWID and will incorporate HIV prevention, harm reduction education, and linkage to care, including HCV treatment [5].

For participants who are randomized to receive the SIRI checklist, providers will receive instructions on how to insert a 5-item checklist into their documentation using a smart phrase text for ease of use and standardization (appendix 2). Because use of a checklist alone has been shown to change provider behavior, providers will not be required to perform any additional tasks other than daily documentation of the checklist. We anticipate that documentation of evidence-based services using a checklist reminder will increase the likelihood that participants will receive them.

The intensive peer intervention will include weekly calls to participants for 4 weeks following discharge. If participants do not respond, peers will make 3 attempts to reach participants at their preferred contact number.

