### Data Sources

We will collect data on stigma, HIV awareness and risk behaviors via electronic surveys; results will be stored in a RedCap database [25]. We will obtain data on sociodemographics and clinical factors, like type of infection and HIV and HCV test results, using data extracted from the Electronic Medical Record (EMR) and managed in a RedCap database. Prescription data and healthcare utilization data will also be obtained from the EMR. We will extract outcomes related to linkage to prescription for PrEP and/or MOUD on discharge, and attendance at provider visit(s) related to HIV and/or addiction services following hospitalization. Data extraction will be limited to services provided in the UAB health system.

Participating providers who serve PWID will be asked to complete a standardized survey of the study and intervention in order to determine the study feasibility and identify opportunities to improve.

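### Referral outcomes read from provider notes can favour the checklist arms through charting alone, because the checklist is itself a note template and no other hospital source is named for referrals

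*Protocol article*

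**What the plan says.** **The efficacy signal.** The progression-criteria text sits under Aim 2 in the Methods. It looks at whether participants received the recommended services, "such as HIV and HCV screening, MOUD prescriptions, and HIV PrEP referrals", and adds: "Specifically, we will evaluate whether these measures are enacted after the inclusion of the smart phrase text". It names two sources: "This data will be collected via provider documentation and the 3-month follow-up survey with participants".

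**The checklist.** The Intervention section states: "For participants who are randomized to receive the SIRI checklist, providers will receive instructions on how to insert a 5-item checklist into their documentation". On workload it says that "providers will not be required to perform any additional tasks other than daily documentation of the checklist". Participants are randomised "into one of the four groups: SIRI Checklist, SIRI Checklist + Enhanced Peer, Enhanced Peer, and Standard of Care", so two of the four arms carry the template.

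**The comparison.** Aim 2 in Study Objectives and Specific Aims covers buprenorphine and PrEP initiation, HCV screening and community referral, and compares them with the groups without the checklist.

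**The other sources.** Data Sources takes clinical factors, "like type of infection and HIV and HCV test results, using data extracted from the Electronic Medical Record (EMR"), from the record. It does the same for prescriptions, utilisation and attended HIV or addiction visits, all within UAB. The Abstract also assigns HIV and HCV testing and MOUD and PrEP prescriptions to EMR data combined with surveys. Neither section names a source for referrals, although the Analysis section lists referral to community care among the outcomes.

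**Adherence.** The progression criteria check use of the smart phrase in the notes and state: "We expect that this smart phrase will be included in all participant documentation after implementation".

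**The concern.** Randomisation to the checklist assigns a charting template, and charting is one of the two named sources for deciding whether a service was received. For any item read from the notes, the intervention alters the measuring instrument on one side of the comparison. A provider in a non-checklist arm may make the same referral and not write it down. This is differential ascertainment, and its likely direction favours the checklist.

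Two things in the text sharpen the problem. Notes also serve to measure adherence, and nothing separates text that shows the template was used from evidence that the service was delivered. And the efficacy signal is judged from the point at which the smart phrase enters the note, a reference point that the non-checklist arms do not have.

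At stake is the reading of the efficacy signal. The progression criteria guide adjustments before a larger study, so a charting artefact could be carried forward as a sign that the checklist changes care.

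**Working it through.** **1. Which source decides each outcome**

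| Outcome | Progression criteria | Abstract / Data Sources | Exposed to the template? |
|---|---|---|---|
| HIV, HCV screening | Notes + survey | EMR test results | Only if scored from notes |
| MOUD prescription | Notes + survey | EMR prescriptions | Only if scored from notes |
| PrEP prescription | Not named (referral only) | EMR prescriptions | Not if taken from the EMR |
| Attended visits | Not named | EMR utilisation | Not if taken from the EMR |
| PrEP referral | Notes + survey | None named | Yes |
| Referral to community care | Not named | None named | Yes, if scored from notes |

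For screening and MOUD the two parts of the article name different sources, and neither is said to prevail. For the two referral items no hospital source outside the notes is named.

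**2. Whether the survey closes the gap**

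Aim 2 describes the 3-month survey as covering PrEP use, addiction treatment and utilisation. Screening and referral are not named. At the 75% retention target it would reach 0.75 × 60 = 45 participants.

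**3. Size of the groups compared**

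The stated total reproduces: 4 × 15 = 60. The checklist comparison is 2 × 15 = 30 against 30.

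**4. Illustrative size of the artefact**

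Assume the same true referral rate *p* in both groups, with a delivered referral charted with probability *s*₁ (checklist) or *s*₀ (no checklist). With no true effect,

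spurious difference = *p* × (*s*₁ − *s*₀).

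All charting rates below are assumptions, since the article gives none.

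- *p* = 0.50, *s*₁ = 0.95, *s*₀ = 0.80: 0.50 × 0.15 = 0.075, or 7.5 points.
- *p* = 0.50, *s*₁ = 0.95, *s*₀ = 0.60: 0.50 × 0.35 = 0.175, or 17.5 points.

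The only service rate in the article is the 37% discharged on MOUD (Standard of Care). Borrowing it as an illustrative *p*, with *s*₁ = 0.95:

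- *s*₀ = 0.85: 0.37 × 0.10 = 3.7 points.
- *s*₀ = 0.70: 0.37 × 0.25 = 9.3 points.
- *s*₀ = 0.50: 0.37 × 0.45 = 16.7 points.

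Incomplete use of the template shrinks the artefact. If it is used for 80% of participants (the article's adherence threshold) and the rest are charted as in the other arms, the first two figures become 0.80 × 7.5 = 6.0 and 0.80 × 17.5 = 14.0 points.

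**5. Comparison with sampling error**

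With 30 per side and *p* = 0.50, the 95% half-width is 1.96 × √(2 × 0.50 × 0.50 / 30) = 0.253, about 25 points. The illustrated artefact is smaller than this. It shifts the point estimate and the whole interval, and the interval does not reveal the shift.

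**6. Under a template-independent source**

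If a service is counted from a record whose completeness does not depend on the template, *s*₁ = *s*₀ and the artefact is *p* × 0 = 0.

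**The case against.** The strongest reply is that most outcomes are already protected. A note template cannot create a laboratory result, a prescription or an attended visit, and the Abstract, Data Sources and Table 1 all point to such measures. This stands. A reader might infer that the whole efficacy comparison, screening and prescribing included, is inflated by charting. The documents do not support that: the artefact is nil for those outcomes if the EMR sources are used as stated.

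Second, the progression text may describe a check within the checklist arms and not a between-arm comparison, and it names the survey as well as the notes. Both are fair. But the Specific Aims compare the same kinds of measure between groups, and the survey as described does not name referral.

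Third, how the template works is partly out of sight. The checklist wording is in an appendix and the red/amber/green thresholds are in a figure, neither of them shown. The smart phrase may be a reminder more than a record of delivery, and the weight of the efficacy signal in progression is unknown. This limits any claim about size. The Intervention section does, however, describe the provider's task as documentation.

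Fourth, item-level abstraction rules often sit in a fuller protocol. Their absence is not the complaint here. The article does state a source for the efficacy signal, that source is altered by the intervention, and it differs from the source in Data Sources.

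Harm reduction counselling is a checklist item but not a listed outcome, so the point does not extend to it.

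**Conclusion.** The concern holds for outcomes read from provider notes, chiefly PrEP referral and referral to community care. These can look better in the checklist arms with no change in care. The direction rests on one assumption: that delivered referrals are charted more completely with the template than without it. The size cannot be derived from the article. The 7.5 to 17.5 points are an illustration that depends wholly on the assumed 50% true rate and the assumed charting rates of 95% against 60 to 80%.

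For screening and MOUD prescribing, the defect is an unreconciled source, not a demonstrated bias.

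The outcomes concerned are exploratory, summarised with descriptive statistics and confidence intervals. The primary feasibility outcome is not affected: recruitment, retention and survey completion do not depend on charting, and extracting checklist documentation is properly a question about the notes.

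A related inconsistency needs settling. The adherence text expects the smart phrase in the documentation of all participants, while the Intervention and Sampling sections confine it to those allocated to the checklist. Read literally, the first leaves no template-free group. It may mean only participants in the checklist arms, but it does not say so.

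The change is worth making before data abstraction.

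**What to change.** 1. Align the signals-of-efficacy text with Data Sources. Count HIV and HCV screening only from laboratory orders or results, and MOUD and PrEP prescribing only from order and prescription records, in all four arms.
2. Count PrEP and community referrals from referral orders or scheduled appointments, supplemented by a participant item in the 3-month survey. Use the same abstraction form in every arm.
3. State that smart-phrase text is evidence of fidelity only and never, on its own, of delivery.
4. Reconcile the adherence statement about all participants' documentation with the sections that restrict the checklist by allocation, and name the denominator for the 80% adherence threshold.

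**Cost.** Test and prescription data are already in the extraction plan. Referral orders and scheduled appointments are not, so one field must be added, along with a survey item and the abstraction wording. Sample size and interventions are unchanged. Verbal referrals, and referrals outside UAB that leave no UAB record, may be missed. This lowers the recorded rate, but there is no reason to expect the loss to differ by checklist allocation.
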